#### Secondary analyses

In a secondary analyses changes diabetes medication during follow-up will be accounted for. Time dependent cox proportional hazard analyses will be used to estimate the adjusted hazard ratio of developing all cancer when using gliclazide compared to other SUs (both individual and grouped as non-gliclazide SU). Exposure to confounders (including concurrent metformin and insulin use) will be handled as time varying variables where follow-up is available. The updated mean method will be used for HbA1c, BMI and serum creatinine. These analyses will be repeated to investigate the adjusted hazard ratio of breast, colorectal, prostate, bladder and lung cancer.

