#### Exposure

Patients will be considered unexposed to SUs until the time of the first SU prescription within ZODIAC. A one-year lag period will be accounted for. A lag period is necessary to take into account a latency time window and to minimise possible detection bias around the time of treatment initiation. Exposure to a SU will be classified according to one of the following, mutually exclusive, categories: gliclazide use, glimepiride use, tolbutamide use, glibenclamide use, non-SU use.

We aim to determine whether there are duration-response relationships between the use of SUs and obesity-related cancer incidence. Duration-response will be assessed in terms of cumulative duration of use, defined as the total number of years of use calculated by summing the durations of yearly prescriptions received between cohort entry and the time of the event and will be used as a time-dependent covariate.

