#### Primary analysis

Descriptive statistics will be used to characterize the patients at cohort entry.

Time dependent cox proportional hazard analyses will be used to estimate the adjusted hazard ratio of developing obesity-related cancer when using gliclazide compared to other SUs (both individual and grouped as non-gliclazide SU). Exposure to SUs will be included as the cumulative number of years exposed to a specific SUs. Exposure status for SU will be updated annually. The primary analyses will be corrected for the previously mentioned confounders measured at baseline.

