#### Missing data

When appropriate, in case of missing data multiple imputation will be used. In case multiple imputation cannot be used (e.g. data are not missing at random or missing completely at random), the updated means method will be used. The updated mean method averages the baseline values with the mean annual values [27]. The updated mean method is similar to the technique used in the UKPDS [28]. When calculating the updated means, we will allow a maximum of 2 consecutive years to be missing, with a maximum of 3 years in the complete follow-up.

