#### Sensitivity analysis

Six sensitivity analyses will be planned for supporting the main analyses. Firstly, because the latency window is uncertain, the primary analyses for within-class differences will be repeated with lag periods of zero and two years. Secondly, the primary analysis will be repeated but the adjusting confounders will be measured at the year before first SU prescription. Thirdly, the main analysis will be repeated but with the exclusion of cancer events 1 year after initiation of a SU. Fourthly, to investigate the accuracy of our results the analysis will be repeated in patients in whom all data on medication are complete. Fifthly, to investigate the accuracy of our results the analysis will be repeated in patients who have no missing data on HbA1c, BMI and serum creatinine. Sixthly, to quantify the effect of patients switching medication within the class of SUs, an intention-to-treat analysis for patients who switch SUs will be performed.

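### The secondary models state no lag for time-varying confounders, so signs of undiagnosed cancer can be adjusted for and can bias the comparison between sulfonylureas

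*Protocol article*

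**What the plan says.** The lag appears in the Exposure section of the protocol article, which deals only with SU use: "A one-year lag period will be accounted for". The reason follows: "A lag period is necessary to take into account a latency time window and to minimise possible detection bias around the time of treatment initiation".

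The Secondary analyses section sets the covariate timing for the all-cancer and site-specific models: "Exposure to confounders (including concurrent metformin and insulin use) will be handled as time varying variables where follow-up is available". It adds: "The updated mean method will be used for HbA1c, BMI and serum creatinine". The Missing data section describes the updated mean as an average of the baseline value and the later annual values, and gives no cut-off before the event. Under Follow-up, observation runs until cancer is diagnosed.

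The primary model differs: "The primary analyses will be corrected for the previously mentioned confounders measured at baseline". The lag sensitivity analysis concerns that model only: "the primary analyses for within-class differences will be repeated with lag periods of zero and two years".

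**The concern.** A lag on exposure acknowledges that a cancer diagnosed this year was probably already present last year, so recent drug use should not be credited with it. The same holds for other measurements taken in that interval. A patient with an undiagnosed tumour may lose weight, show worsening HbA1c and be started on insulin. In a model that enters these values without a lag, they are partly results of the outcome rather than causes of it.

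A non-causal association between insulin and cancer then appears. If users of one SU start insulin less often than users of another, adjusting for insulin passes part of that association to the SU contrast. The contrast can move away from the truth even when neither SU nor insulin affects cancer. What is at stake is the gliclazide comparison for all cancer, and for those separately analysed sites where such a prodrome occurs.

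**Working it through.** **Which models and checks are exposed**

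| Element | Covariate timing stated | Lag on covariates |
|---|---|---|
| Primary model | Baseline | Not needed |
| Secondary models: metformin, insulin | Time-varying | None stated |
| Secondary models: HbA1c, BMI, creatinine | Updated mean | None stated |
| Zero- and two-year lag analyses | Primary model, baseline covariates | Not applicable |

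The other sensitivity analyses do not fill the gap. One re-times the confounders of the primary model to the year before the first SU prescription. One drops cancers in the year after SU initiation, which is not the year before diagnosis. Two restrict to complete data, and one handles switchers by intention to treat. None lags a time-varying covariate.

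**Size**

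The article states no event count, effect size or power, so there is no figure to reproduce. The mechanism was checked by simulation. All inputs are assumptions:

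- 300,000 patients, averaged over 3 seeds, half on gliclazide, with annual visits.
- Preclinical onset about 1.2% per year, diagnosis in the following year. BMI has a true hazard ratio of exp(0.03) = 1.03 per kg/m². Insulin has no true effect.
- Insulin starts at 4% per year on other SUs. On gliclazide the rate is multiplied by 1.0 or by 0.6 (0.6 × 4% = 2.4% per year).
- Preclinical cancer multiplies insulin starts by 1, 2, 4 or 8 and lowers BMI by 0, 1.5 or 3 kg/m².
- Model: complementary log-log hazard (grouped Cox) with gliclazide, insulin ever started, updated-mean BMI and year. Covariates are taken at the latest visit (unlagged) or one year earlier (lagged).

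| True HR | Insulin-start ratio | Prodrome: insulin × / BMI drop | Gliclazide HR, lagged | Gliclazide HR, unlagged | Insulin HR, lagged | Insulin HR, unlagged |
|---|---|---|---|---|---|---|
| 1.00 | 0.6 | 1 / 0 | 1.001 | 1.002 | 1.009 | 1.013 |
| 1.00 | 1.0 | 4 / 1.5 | 1.001 | 1.000 | 1.004 | 1.675 |
| 0.80 | 1.0 | 4 / 1.5 | 0.804 | 0.803 | 1.012 | 1.690 |
| 1.00 | 0.6 | 2 / 1.5 | 1.001 | 1.018 | 1.009 | 1.209 |
| 1.00 | 0.6 | 4 / 1.5 | 1.001 | 1.049 | 1.009 | 1.643 |
| 1.00 | 0.6 | 8 / 3 | 1.001 | 1.116 | 1.009 | 2.791 |
| 0.80 | 0.6 | 4 / 1.5 | 0.805 | 0.843 | 1.014 | 1.653 |
| 0.80 | 0.6 | 8 / 3 | 0.805 | 0.897 | 1.014 | 2.825 |

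Relative shift = unlagged ÷ lagged − 1. The largest is 1.116 / 1.001 − 1 = 11.5%, or about 12%. In the last row the apparent risk reduction falls from 1 − 0.805 = 19.5% to 1 − 0.897 = 10.3%.

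The first three rows give the boundary conditions. Without a prodrome, or without a difference between SUs in insulin start, the SU hazard ratio does not move, even where the insulin hazard ratio is badly wrong.

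Updated means dilute late values. In a running mean of n values, a final drop of d enters as d/n; with n = 6 and d = 1.5 that is 0.25 kg/m². Even so, the unlagged BMI hazard ratio fell from 1.03 to between 1.01 and 1.02 in the prodrome scenarios.

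A second set-up used a pooled logistic model, no true effects, insulin starts of 2% per year on gliclazide and 5% on other SUs, and a 3- or 5-fold prodrome. It gave unlagged gliclazide odds ratios of 1.04 and 1.11, against 0.99 lagged (1.04 / 0.99 = 1.05 and 1.11 / 0.99 = 1.12). A larger run of that set-up gave 1.07 and 1.14. The gap of 0.03 between the runs is compatible with simulation noise: the lagged estimates themselves vary between 0.99 and 1.01 around a true value of 1.00.

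**The case against.** The strongest reply is that the point rests on silence. The article never says that covariates run up to the cancer date, and a condensed article may leave time indexing to a fuller plan. The word used for metformin and insulin may simply mean co-medication taken alongside an SU, which could sit in the same lagged year. This stands in part: no reader can claim that unlagged values will certainly be used. But the article does set covariate timing in the secondary models, and does so without the protection that it calls necessary for SU exposure. A fuller plan that lagged them would have to qualify the sentence as written.

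Second, the stated reasons for the lag are latency and detection bias, not reverse causation through weight loss or insulin start. That is so, but a latency window implies that the tumour is present before diagnosis, and this is all the mechanism needs.

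Third, the size is chosen, not derived. This stands. In the larger run of the second set-up, confining the prodrome to a quarter of cancers (assumed) reduced the odds ratios to 1.02 and 1.04, against 1.01 with lagged insulin. If annual recording misses half of the prodromal effect, the 5-fold case falls from 1.14 to 1.07. HbA1c, metformin and creatinine were not simulated.

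A reader might infer that the SU hazard ratios will be distorted, and for every secondary endpoint. The document does not support that. Both comparison groups use SUs, so bias needs a difference between individual SUs as well as a prodrome, and nothing shows a metabolic prodrome at breast, prostate or bladder. Pancreatic cancer, an obvious candidate, counts only within all cancer. The Background does make a difference between SUs plausible: it suggests lower insulin levels with gliclazide and links several glucose-lowering agents to weight gain.

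**Conclusion.** The point holds as a risk confined to the secondary models. As written, these models can condition on consequences of undiagnosed cancer, and no planned sensitivity analysis would reveal it. Bias in the gliclazide contrast requires both a prodrome that changes insulin use, weight or HbA1c, and a difference between SUs in one of these.

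Under the assumed inputs the shift runs from about 0% to 12%. That range illustrates the mechanism. It is neither an estimate for this cohort nor an upper bound. In the scenarios run, gliclazide users started insulin less often and the bias was upward, hiding part of a benefit; by the same reasoning it would reverse if they started insulin more often. Lagging the covariates by one year returned the SU hazard ratio to the truth in every scenario, but there diagnosis always came within a year of onset. The primary analysis is unaffected.

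**What to change.** In Secondary analyses, state that metformin use, insulin use and the updated-mean HbA1c, BMI and serum creatinine are lagged by the same one year as SU exposure, so that values from the year before the event do not enter the main secondary models.

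In Sensitivity analysis, add an unlagged and a two-year-lag version of the secondary models, with covariates and SU exposure shifted together. The existing zero- and two-year lag analyses cannot serve, because the primary models have no time-varying confounders to shift.

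The change takes two sentences and a shift of the covariate index in the dataset. No new data are needed. The downside is that covariates are one year older, so adjustment for very recent treatment changes, which these analyses are meant to capture, is slightly weaker. The unlagged version shows how much that matters.

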#### Missing data

When appropriate, in case of missing data multiple imputation will be used. In case multiple imputation cannot be used (e.g. data are not missing at random or missing completely at random), the updated means method will be used. The updated mean method averages the baseline values with the mean annual values [27]. The updated mean method is similar to the technique used in the UKPDS [28]. When calculating the updated means, we will allow a maximum of 2 consecutive years to be missing, with a maximum of 3 years in the complete follow-up.

#### Subgroup analyses

In subgroup analyses effects of exposure to BMI and HbA1c during follow-up and the relation between SUs and cancer will be investigated and interaction will be tested. A second subgroup analysis will investigate cancer risk in patients who do and do not use metformin in combination with an SU.

#### Sensitivity analysis

Six sensitivity analyses will be planned for supporting the main analyses. Firstly, because the latency window is uncertain, the primary analyses for within-class differences will be repeated with lag periods of zero and two years. Secondly, the primary analysis will be repeated but the adjusting confounders will be measured at the year before first SU prescription. Thirdly, the main analysis will be repeated but with the exclusion of cancer events 1 year after initiation of a SU. Fourthly, to investigate the accuracy of our results the analysis will be repeated in patients in whom all data on medication are complete. Fifthly, to investigate the accuracy of our results the analysis will be repeated in patients who have no missing data on HbA1c, BMI and serum creatinine. Sixthly, to quantify the effect of patients switching medication within the class of SUs, an intention-to-treat analysis for patients who switch SUs will be performed.

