#### Exclusion

Patients treated with long-acting or mixed insulin before oral glucose lowering agents and those receiving insulin on top of SU at study entry will be excluded. Patients who received a cancer diagnosis before receiving a SU will be excluded. For the main analyses patients who switch medication within the class of SUs will be excluded at the time the switch occurs.

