#### Co-variates

Co-variates collected at cohort entry and annually thereafter are: age, sex, year of cohort entry, HbA1c (continuous), diabetes duration (time between diabetes diagnosis and cohort entry, continuous), BMI (continuous), serum creatinine (continuous), metformin use (yes, no), insulin use (yes/no), history of cancer (no non-melanoma skin cancer) (yes, no) and smoking (ever, never, unknown).

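### The fourth sensitivity analysis keeps only patients with complete medication records, which selects on length of follow-up and can shift the hazard ratio if missingness or follow-up differs between SUs

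*Protocol article*

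**What the plan says.** Under Sensitivity analysis, the fourth of six supporting analyses restricts the population: "to investigate the accuracy of our results the analysis will be repeated in patients in whom all data on medication are complete". The fifth does the same for three covariates: "the analysis will be repeated in patients who have no missing data on HbA1c, BMI and serum creatinine". Both are presented as checks on the accuracy of the results.

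Four other statements decide how these rules act:

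- Primary analysis: "Exposure status for SU will be updated annually".
- Co-variates: the list opens with "Co-variates collected at cohort entry and annually thereafter are" and includes HbA1c, BMI, serum creatinine and year of cohort entry.
- Follow-up: observation ends at a cancer diagnosis; otherwise at death, end of ZODIAC registration or 31 December 2012.
- Exclusion: "For the main analyses patients who switch medication within the class of SUs will be excluded at the time the switch occurs".

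Covariate timing differs by analysis. For the primary model, "The primary analyses will be corrected for the previously mentioned confounders measured at baseline". For the secondary models, "The updated mean method will be used for HbA1c, BMI and serum creatinine".

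**The concern.** With annual records, a patient diagnosed with cancer in year 2 needs about two complete records to be kept, while a cancer-free patient followed for ten years needs about ten. A rule that demands completeness over all of follow-up therefore decides who enters at baseline by what happens later, and favours short follow-up. This raises the apparent cancer hazard among those kept. If it is raised by a different factor in one SU group than in another, the hazard ratio moves even though the drugs do not differ.

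At stake is the meaning of the check. A disagreement with the main result would be read as a sign that missing data matter, when the selection rule may have produced it. An agreement could likewise arise because two distortions cancel.

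**Working it through.** **Inputs.** From the Protocol article: annual recording, follow-up ending at cancer, censoring at an SU switch, a window from 1998 to 2012, and a hazard ratio as the estimand. The article gives no missing-data rate, switching rate, cancer rate or complete-record result, so there is no stated figure to reproduce. All rates below are assumptions.

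**Step 1: closed form.** Let L be the cancer hazard, c the hazard of any other exit, q the yearly chance that a record is missing, and m = −ln(1 − q). A patient is kept if no record goes missing before follow-up ends. Among those kept, time to the end of follow-up has hazard L + c + m, and a fraction L/(L + c) of the endings are cancers. The apparent cancer hazard is therefore

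L × (L + c + m)/(L + c) = L × [1 + m/(L + c)].

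With a true hazard ratio of 1, the complete-record hazard ratio is [1 + m₁/(L + c₁)] / [1 + m₀/(L + c₀)].

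- Equal m and equal c: the ratio is exactly 1.
- L = 0.01, c = 0.04 in both groups, q = 0.10 versus 0.05: m = 0.1054 and 0.0513; (1 + 0.1054/0.05)/(1 + 0.0513/0.05) = 3.107/2.026 = 1.53.
- L = 0.01, q = 0.10 in both groups, c = 0.04 versus 0.10: (1 + 0.1054/0.05)/(1 + 0.1054/0.11) = 3.107/1.958 = 1.59.

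The formula gives the direction: the SU with more missing records, or with less exit by other routes, looks worse. It overstates the size, because it has no common administrative end of study. Simulation gives the size.

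**Step 2: simulation with an administrative end.** 3,000,000 patients per scenario, true hazard ratio 1, L = 0.01, other exit 0.04 per year unless stated, planned follow-up 1–15 years unless stated.

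| Scenario | Hazard ratio (95% CI) |
|---|---|
| No selection | 1.009 (1.000–1.019) |
| Equal follow-up, q = 0.05 in both | 1.008 (0.998–1.018) |
| Equal follow-up, q = 0.10 in both | 0.993 (0.982–1.004) |
| Equal follow-up, q = 0.20 in both | 1.001 (0.987–1.015) |
| q 0.12 vs 0.10 | 1.086 (1.073–1.099) |
| q 0.10 vs 0.05 | 1.230 (1.217–1.243) |
| q 0.20 vs 0.10 | 1.470 (1.452–1.489) |
| q = 0.10 in both; other exit 0.04 vs 0.10 per year | 1.090 (1.077–1.104) |
| Missingness depends only on an adjusted covariate | 1.002 (0.992–1.012) |
| Completeness required at baseline only, q 0.20 vs 0.10 | 1.002 (0.992–1.012) |

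In the three equal scenarios the absolute cancer rate rises from 0.010 to 0.012, 0.016 and 0.024 per year, and 72%, 53% and 30% of patients are kept.

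**Step 3: switch censoring.** 4,000,000 patients per scenario, cancer hazard 1.2% per year, records missing completely at random, same entry years in both groups, standard error about 0.005. The ratio is the less-switched SU over the more-switched SU; the true value is 1.00.

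| Switch censoring per year | 5% of records missing | 10% missing |
|---|---|---|
| 2% vs 10% | 1.06 | 1.12 |
| 2% vs 15% | 1.08 | 1.17 |

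A separate run agreed to within 0.01.

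**Step 4: entry period.** With mean planned follow-up of 5 versus 7 years, the unadjusted ratio is 0.92 at 5% missing and 0.84 at 10%. Year of cohort entry is a listed covariate, and adjusting for it largely absorbs this source, so it is not counted in the size of the problem.

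**Step 5: the alternative rule.** Censoring at the first missing record gave 0.993 (0.980–1.006) with q 0.20 versus 0.10, 1.005 (0.993–1.018) with differing entry periods, and 0.99–1.01 in the switching scenarios.

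**The case against.** A reader might infer that both analyses give a hazard ratio away from 1 whenever data are missing at random and the SUs do not differ. The documents do not support that. With equal missingness and equal follow-up the ratio stays at 1, and it also does so when missingness depends only on an adjusted covariate. The article does not say that missingness, exit or switching differs by SU. The Background notes that the Dutch guideline prefers gliclazide, which makes different switching plausible but supplies no figure. This objection stands, and the point is conditional for that reason.

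A reader might also charge the fifth analysis with the same defect. The primary model uses baseline covariates, so repeating it in patients without missing HbA1c, BMI or creatinine may well mean complete baseline values, which gives no bias. Against that, the Background says the primary aim accounts for weight change during follow-up, and the secondary models use updated means. The text leaves the time point open, so this is an ambiguity and not an established error.

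The simulations compare fixed groups, whereas the plan models cumulative years of use. That is a fair limit on the exact size. When the ratio was expressed per year since start, the 0.04 versus 0.10 exit scenario still showed a shift, 1.012 per year (1.009–1.015).

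Finally, complete-record analyses are conventional and a condensed article may leave detail to a fuller plan. For the fourth analysis, however, the article states the selection rule itself. With exposure updated annually, its natural reading is completeness over all of follow-up.

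**Conclusion.** The point holds in conditional form for the fourth analysis. Selecting patients on complete medication records over follow-up can produce a hazard ratio away from 1 with no true SU difference, provided that missingness or follow-up differs between SUs after adjustment. Adjusting for year of cohort entry does not remove the part that comes from censoring at a switch. That part is about 1.06 to 1.17 under the assumed 1.2% yearly cancer hazard, 5–10% yearly missingness and 2% versus 10–15% yearly switching. Missingness that itself differs by SU adds a second route, with 1.09 for 12% versus 10% per year and 1.23 for 10% versus 5%. None of these rates is in the documents, and a shorter planned follow-up would bring the figures closer to 1.

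The fifth analysis is affected only if completeness is required beyond baseline. It would be wrong to infer that the main finding is compromised: these are two supporting analyses and the primary result does not depend on them.

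**What to change.** **Fourth analysis.** Replace the patient-level restriction with a time-based one: each patient contributes follow-up while the annual medication record is complete and is censored at the first missing record. Plain censoring assumes that a gap says nothing about cancer risk given the model. If missingness depends on measured values, add inverse-probability-of-censoring weights built from the last recorded values.

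**Fifth analysis.** State the time point. For the baseline-adjusted primary model, require complete HbA1c, BMI and serum creatinine at baseline only. For models with time-varying covariates, censor at the first missing value.

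**Cost.** Two sentences and a changed data step. Some patients contribute shorter follow-up, and one whose first record is already missing contributes none. In return, patients with a later gap are no longer lost altogether; in the equal scenario with 10% of records missing per year, the restriction would drop 47% (1 − 0.53).
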